## Abstract

**Background:**

The prevalence of hypertension among people with chronic kidney disease is high with over 60% of people not attaining recommended targets despite taking multiple medications. Given the health and economic implications of hypertension, additional strategies are needed. Exercise is an effective strategy for reducing blood pressure in the general population; however, it is not known whether exercise would have a comparable benefit in people with moderate to advanced chronic kidney disease and hypertension.

**Methods:**

This is a parallel-arm trial of adults with hypertension (systolic blood pressure greater than 130 mmHg) and an estimated glomerular filtration rate of 15–45 ml/min 1.73 m^2^. A total of 160 participants will be randomized, with stratification for estimated glomerular filtration rate, to a 24-week, aerobic-based exercise intervention or enhanced usual care. The primary outcome is the difference in 24-h ambulatory systolic blood pressure after 8 weeks of exercise training. Secondary outcomes at 8 and 24 weeks include: other measurements of blood pressure, aortic stiffness (pulse-wave velocity), change in the Defined Daily Dose of anti-hypertensive drugs, medication adherence, markers of cardiovascular risk, physical fitness (cardiopulmonary exercise testing), 7-day accelerometry, quality of life, and adverse events. The effect of exercise on renal function will be evaluated in an exploratory analysis. The intervention is a thrice-weekly, moderate-intensity aerobic exercise supplemented with isometric resistance exercise delivered in two phases. Phase 1: supervised, facility-based, weekly and home-based sessions (8 weeks). Phase 2: home-based sessions (16 weeks).

**Discussion:**

To our knowledge, this study is the first trial designed to provide a precise estimate of the effect of exercise on blood pressure in people with moderate to severe CKD and hypertension. The findings from this study should address a significant knowledge gap in hypertension management in CKD and inform the design of a larger study on the effect of exercise on CKD progression.

**Trial registration:**

ClinicalTrials.gov, ID: NCT03551119. Registered on 11 June 2018.

**Electronic supplementary material:**

The online version of this article (10.1186/s13063-019-3235-5) contains supplementary material, which is available to authorized users.

## Background

In people with chronic kidney disease (CKD), hypertension is an important modifiable risk factor for both cardiovascular (CV) events and progressive renal dysfunction [1–5]. Delaying the progression of CKD is important because it enables patients to live longer without significant complications from CKD (malnutrition, bone and electrolyte disorders, anemia, higher risk of CV events) and the need for renal replacement therapy. Despite the significance of attaining blood pressure (BP) targets, the estimated prevalence of hypertension among clinical populations with CKD remains high at 67–86% [6, 7]. This is despite the use of multiple anti-hypertensive drugs and access to dietary counseling on low sodium intake (more than 90% of Canadian CKD clinics have a dietician on staff) [8].

Regular exercise is effective in reducing BP in people without CKD. BP reduction with regular aerobic exercise ranges from − 3.5 to − 6.1 mmHg/− 2.5 to − 3.0 mmHg [9–11]. Although guidelines for the management of CKD recommend exercise for CV health, randomized trials in people with impaired estimated glomerular filtration rate (eGFR) and hypertension are limited [12, 13]. In addition, compared to those with normal kidney function, people with CKD are more likely to need multiple anti-hypertensive drugs to attain BP targets [14, 15], suggesting that responsiveness to other approaches may also be reduced. As a result of this knowledge gap, exercise resources are not offered in the routine multidisciplinary care of people with CKD and the prevalence of sedentary behavior remains double that of the general population [8, 16].

The primary objective of this trial is to determine the efficacy of an 8-week, aerobic-based exercise intervention on systolic blood pressure (SBP) in people with moderate to severe CKD. We hypothesize that participants allocated to the exercise intervention will achieve a significant mean reduction in SBP as measured by the “gold standard,” 24-h ambulatory blood pressure (ABPM) compared to control. Results from this efficacy trial will also be used to inform the design of a larger, multi-center trial aimed at evaluating the effect of exercise on the risk of CKD progression.

### Objectives

#### Primary objective

The primary aim of this study is to determine the efficacy of an 8-week exercise intervention on SBP in people with moderate to severe CKD.

#### Secondary objective

The secondary objective is to evaluate the effect of exercise on other measures of BP: aortic stiffness, changes in the required dose of anti-hypertensive drugs, markers of CV risk, cardiorespiratory fitness, a physical activity, quality of life (QoL), and adverse events (AEs) at 8 and 24 weeks.

#### Tertiary objective

The tertiary objective is to inform the design of a larger, multi-center, randomized controlled trial (RCT) examining the effect of exercise on the progression of CKD; specifically, to establish trial processes, feasibility, and to estimate the variance of the treatment effect for eGFR.

## Methods

### Design, setting, and participants

The flow of participants through the trial is summarized in Fig. 1. Participants will be randomized to either an aerobic-based exercise intervention or a control. Participants will be recruited from both academic and community-based clinics within Alberta Kidney Care (AKC) North. AKC North is a single, provincially funded renal program in Edmonton, AB, Canada. The University of Alberta Research Ethics Board approved this protocol (Pro00078564). The study was prospectively registered (NCT0355119). The Standard Protocol Items: Recommendations for Interventional Trials (SPIRIT) Checklist is available as an additional document (Additional file 1).

**Fig. 1 Fig1:**
[figure not shown]
Flow of participants through the trial

### Recruitment and eligibility

A range of recruitment strategies will be employed, including direct recruitment from AKC North CKD clinics by study staff, posters, advertising through the local branch of The Kidney Foundation, and referrals from physicians and renal clinic staff. All recruitment materials and participant information has been co-developed or reviewed with a panel of patient advisors. Prior to eligibility screening, informed written consent will be obtained by the trial study coordinator from the potential participant.

#### Inclusion

Eligible patients are those aged 18 years or older, with hypertension, who are followed in an Edmonton-based CKD clinic with an eGFR between 15 and 44 ml/min per 1.73m^2^ on two occasions in the past year. Hypertension is defined as a resting SBP greater than 130 mmHg on screening measurement with a validated, electronic sphygmomanometer (Omron HEM-907XL (Omron Healthcare, Kyoto, Japan)), using the mean of three readings after discarding the first reading and at least one previous SBP measurement above 130 mmHg on a separate occasion within the past 6 months (home or clinic measurement). Although there is evidence that lower SBPs are beneficial, there is still debate regarding the optimal BP target in people with CKD [17, 18] and a target SBP of less than 130 mmHg is consistent with current Canadian CKD Management Guidelines [19]. Additional inclusion criteria are: able to ambulate with or without an assistive device for at least three consecutive minutes, capable of providing informed consent, English language sufficient to understand written information and comply with the testing and interventions, and approval of the attending nephrologist.

#### Exclusion

Resting SBP greater than 160 mmHg or resting DBP greater than 110 mmHg on screening BP clinic measurement, changes to BP medications within the past 8 weeks, arm circumference greater than 54 cm (size limit of large ABPM cuff), recent (within 6 weeks) or planned (within 6 months) major CV events or procedures, any absolute contraindication to exercise (American College of Sports Medicine Guidelines) [20], pregnant or planning to become pregnant within the next 9 months, life expectancy or predicted time to renal replacement therapy less than 12 months (attending physician judgment), planned move or hospital admission within the next 9 months, currently enrolled in an interventional clinical trial or a structured exercise program, significant barriers to participation (e.g., no available transportation to the training facility), solid organ transplantation, taking other medications known to affect BP (prednisone/cyclosporine) with expected adjustment in the next 9 months. Patients will be excluded from the study if exercise testing results preclude safe exercise training as defined by the American College of Cardiology/American Heart Association (ACC/AHA) guidelines [21], e.g., abnormal BP response, early ischemic changes, and unexpected life-threatening arrhythmia. The trial cardiologists will review the electrocardiogram at peak exercise on all participants.

### Randomization and blinding

Participants will be randomized (1:1) to enhanced usual care (measurement of physical activity levels) or the exercise intervention. A randomized permuted block design (of 4 and 6) will be used. To optimize comparability of the two groups at baseline, randomization will be stratified by baseline eGFR (15–29 ml/min/1.73m^2^ and 30–44 ml/min/1.73m^2^). The randomization sequence will be computer generated using Stata/MP 15.1 (https://www.stata.com/) and allocation will be concealed by web-based central randomization using the Research Electronic Data Capture System (REDCap 8.8.2© 2018 Vanderbilt University). Due to the nature of the intervention, participants cannot be blinded to group assignment; however, the primary outcome is objectively measured (24-h ABPM).

### Intervention arms

#### Exercise group

All participants will receive standard care according to the Canadian Guidelines for the Management of Chronic Kidney Disease [19]. Those allocated to the intervention group will participate in a 24-week exercise program delivered in two phases. Phase 1 is an 8-week program of once weekly, supervised, facility-based exercise sessions and twice-weekly, home-based sessions. The weekly, facility-based sessions will take place in a rehabilitation facility at the University of Alberta Hospital. Phase 2 is a 16-week, home-based exercise program, overseen by a kinesiologist. During this phase, participants will be progressed through their home-based exercise program from phase 1 on an individualized basis. In phase 2, participants are seen once by the kinesiologist, 4 months after study start (in the middle of the 16-week home phase) and as needed. The exercise intervention is primarily aerobic, as the BP-reducing effect of exercise is greater with aerobic versus dynamic resistance exercise in people with hypertension: − 8.3 (95% CI − 10.7, − 6.0)/5.2 (95% CI − 6.8, − 3.4) mmHg versus 0.47 (95% CI − 4.4, 5.3)/− 1.0 (95% CI − 3.9, 1.9) mmHg [9]. The mode of aerobic exercise (e.g., walking, cycling) will be individualized based on participant preference and feasibility for home. In both phases, participants will be prescribed exercise on a minimum of 3 days per week at a moderate intensity (50–60% heart rate reserve) based on the most recent cardiopulmonary exercise test (CPET). Participants will progress over phase 1 to accumulate 150 min of exercise per week [22]. Sessions may be continuous or interspersed as 10-min bouts [23–25]. In both phases, aerobic exercise will be supplemented with isometric resistance exercises (sustained muscle contraction with no change in muscle length). In both hyper- and normotensive populations, isometric resistance exercise is associated with change in SBP of − 6.8 (95% CI, − 7.9 to − 5.6) mmHg [26]. Isometric exercise is also feasible for the home setting and has shown to be safe in people with hypertension using the appropriate technique [27]. Isometric exercises will focus on large muscle groups. The period of time and the postures will be individualized and progressed over the course of the study period.

#### Control group (enhanced usual care)

Renal healthcare providers will continue their usual practice for all trial participants. Participants in the control group will also perform 7-day accelerometry. This is enhanced usual care because physical activity measurement is not routinely performed in CKD clinics. Accelerometry has been associated with increased levels of physical activity; however, this effect is transient and the health impact of activity monitoring is unclear [28]. Furthermore, this approach is critical for recruitment and retention in the control arm and to determine whether participants in the control arm increase their levels of physical activity. The control-arm participants will only receive their accelerometry data after they have completed the study.

### Adherence

To maximize adherence to exercise in the intervention group, we will apply the core set of determinants for behavior change from Bandura’s Social Cognitive Theory: knowledge of health benefits, self-efficacy (expectations about the ability to perform the behavior successfully) and outcome expectations (perceived consequences of the behavior) [29]. Strategies to increase self-efficacy for physical activity will be evidence-based (i.e., vicarious experience and formalized comparative feedback) [30]. The Self-efficacy for Exercise (SEE) scale will be used to evaluate participants’ self-efficacy expectations of exercise expectations [31]. Throughout the trial, the kinesiologist will use motivational interviewing techniques to identify and reinforce the participant’s goals and reasons for changing behavior. To assess adherence and to provide additional motivation, the trial kinesiologist will phone intervention participants every 2 weeks in phase 2. To promote retention, all participants who complete the trial will be offered an additional counseling session with the study kinesiologist and an activity-tracking device. These incentives are intended to assist control-arm participants with increasing their levels of physical activity. For members of the intervention group, these incentives are intended to support the maintenance of physical activity levels.

### Variables and their measurement

#### Baseline clinical information and study visits

A summary of the study schedule is shown in Table 1. Clinical data including cause of CKD, comorbidities, and medications will be collected via participant interviews, chart reviews, and reviews of clinical databases at the baseline study visit. Follow-up study visits are scheduled at 8 and 24-weeks. All participants will be contacted by phone every 2 weeks during the first 8 weeks of the trial to collect data on unscheduled visits and phone calls to healthcare providers, AEs, and changes to anti-hypertensive drugs. Over weeks 8 to 24, participants will be phoned every 4 weeks for this information. Data on AEs and medication changes will be verified using the electronic health repository.

**Table 1 Tab1:** Overview of trial outcomes by study visit

Outcome measure	Method	Baseline	Study visit 1 8 weeks	Study visit 3 24 weeks
Blood pressure	24-h ABPM Clinic BP with an automated oscillometric device	X	X	X
Anti-hypertensive dosing	Tabulated using the Defined Daily Dose (DDD)	X	X	X
Aortic stiffness	Pulse-wave velocity	X	X	X
Medication adherence	Questionnaire	X	X	X
Markers of cardiovascular risk Lipids, HgA_1_C, C-reactive protein Albuminuria, sodium intake Body composition	Blood samples Spot urine sample Bioimpedance spectroscopy, BMI	X	X	X
Cardiorespiratory fitness	Cardiopulmonary exercise testing Six-min Walk Test	X	X	X
Physical activity	7-day accelerometry IPAQ-SF	X	X	X
Quality of life	KDQoL-36 EQ-5D	X	X	X
Self-efficacy	Self-efficacy for Exercise scale	X	X	X
Adherence	7-day accelerometry Participant logbook		X	X
Adverse events	Self report and health record verification	X	X	X

Baseline data is collected prior to randomization. Adverse events are also collected by phone follow-up every 2 weeks for the first 8 weeks and every 4 weeks from weeks 8 to 24

Abbreviations: *ABPM* ambulatory blood pressure monitoring, *BMI* Body Mass Index, *BP* blood pressure, *EQ-5D* EuroQol Health Questionnaire, *HgA*_*1*_*C* hemoglobin A_1_C, *IPAQ-SF* International Physical Activity Questionnaire Short Form, *KDQoL-36* The Kidney Disease and Quality of Life Instrument*,*

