##### Changes in anti-hypertensive drugs

The Defined Daily Dose (DDD) of anti-hypertensive drugs will be used to calculate any changes to BP medications during the study [37]. Medication lists will be collected from the participant and verified with the pharmacy record (available through an electronic provincial data repository) at each study visit. At study visits, a brief questionnaire designed to capture both intentional and non-intentional medication adherence will be administered [38].

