##### Adverse events

Adverse events (AEs) are defined as any unfavorable or unintended event affecting study participants. Major AEs include death, hospitalization (unplanned), emergency department visits, CV events (stroke, myocardial infarction); doubling of serum creatinine from baseline; permanent disability; syncope, arrhythmia. Minor AEs include symptomatic hypoglycemia, hyper- or hypotension requiring medical attention, musculoskeletal injury, pre-syncope during or within 1 h after exercise. Due to the low risk of the intervention we will not use a data safety and monitoring board. All serious adverse events will be forwarded to a physician who is not involved in the trial. The physician will adjudicate whether the event was due to the exercise treatment, facilitate the necessary medical follow-up, and determine whether participation should be modified.

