### Sample size

The sample size calculations for this trial are based on data from exercise and lifestyle modification trials in hypertensive populations [49–51]. As a 5-mmHg reduction in BP in high-risk patients reduces CV events by 15% [52], this study is powered to detect a clinically important difference in mean SBP of 5 mmHg between the intervention and the control groups. Using a two-sample *t* test, alpha 0.05, beta 0.2, and assuming a common standard deviation of 10 mmHg, 128 patients are required. Assuming 20% drop out, 160 patients will be enrolled (80 per group). This sample size is also powered to detect a clinically meaningful difference of 5 points in the KDQOL-36 (alpha 0.05, beta 0.2, and assuming a common standard deviation of 10 points) [53].

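### Adverse events rest on self-report with the health record as a check, so major events after loss of contact may be missed

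*Protocol article*

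**What the plan says.** The AE method is described in three places in the protocol article.

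- **Baseline clinical information and study visits.** Phone calls are the stated route between visits: "All participants will be contacted by phone every 2 weeks during the first 8 weeks of the trial to collect data on unscheduled visits", along with calls to providers, AEs and drug changes. Then: "Over weeks 8 to 24, participants will be phoned every 4 weeks for this information". The section closes with "Data on AEs and medication changes will be verified using the electronic health repository".
- **Table 1, adverse events row.** The method is given as "Self report and health record verification", at baseline, 8 and 24 weeks.
- **Adverse events.** The events that matter most are listed first: "Major AEs include death, hospitalization (unplanned), emergency department visits, CV events (stroke, myocardial infarction". The list continues with creatinine doubling, permanent disability, syncope and arrhythmia.

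Under Statistical analysis, all analyses are by intention to treat, and AEs are tabulated and compared between arms with Fisher's exact test. Under Sample size the drop-out allowance reads: "Assuming 20% drop out, 160 patients will be enrolled (80 per group".

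**The concern.** Self-report works only while someone can be reached. A participant who has died, is in hospital or has left the trial may report nothing, and a check of reported events then has nothing to check. Yet the leading major AEs are ones for which a health record is a natural source without any contact with the participant.

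Two features raise the stakes. The trial is open-label, so the reasons for leaving can differ between the exercise and control arms, and any loss of events can differ with them. No other stated safeguard finds such events either: there is no data safety and monitoring board, and the independent physician sees only the serious events that are forwarded. AEs are a secondary outcome at 8 and 24 weeks, so an incomplete count would feed directly into a reported comparison.

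**Working it through.** **1. The passages side by side.**

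| Data | Stated source | Role of the record |
|---|---|---|
| Baseline clinical data | Interviews, charts, clinical databases | A collection source |
| Drug lists | Participant | "verified with the pharmacy record (available through an electronic provincial data repository) at each study visit" |
| AEs | Phone calls and visits | Verification |

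The first and third rows come from the same section. It makes records a collection source for baseline data and gives them a verifying role for AEs, and Table 1 repeats that role. For drugs the check is tied to a study visit, which a participant who has left does not have. For AEs no timing is given. No section says that the repository is searched for unreported events, or that AE follow-up continues or stops at drop-out.

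**2. How a missed event enters the analysis.** With everyone randomized in the denominator, a participant with no recorded event is a non-event. The multiple imputation is described for the blood-pressure model and draws on 8-week control values. It does not address AEs.

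**3. The plan's own figure.** Inputs from Sample size: difference 5 mmHg, SD 10 mmHg, alpha 0.05 (taken as two-sided), power 80%.

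- Normal approximation: n per arm = 2 × (10/5)² × (1.960 + 0.842)² ≈ 62.8, so 63 per arm (126 in total).
- Exact two-sample t test: 63.77, so 64 per arm and 128 in total, as stated.
- Allowance: 128 / (1 − 0.20) = 160, as stated. Hence 160 × 0.20 = 32, or 16 per arm if balanced.

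The sample size is correct. The 32 are an allowance for the blood-pressure comparison.

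**4. Illustrations (assumed).** The document gives no AE rate and no timing of drop-out.

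- *Follow-up time.* If 32 participants lose all contact at week 12 on average, 32 × 12 = 384 of 160 × 24 = 3,840 person-weeks are uncovered (10%). The extreme, all at the outset, is 32 × 24 = 768 (20%).
- *Upper bound on participants with an event.* Suppose the 32 contribute no AE data at all. With risk p in the other 128 and r × p in the 32, the share missed is 32r / (128 + 32r).

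| p | r | Missed | True total | Share |
|---|---|---|---|---|
| 10% | 1 | 3.2 | 16.0 | 20% |
| 30% | 1 | 9.6 | 48.0 | 20% |
| 10% | 2 | 6.4 | 19.2 | 33% |
| 30% | 2 | 19.2 | 57.6 | 33% |

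- *Unequal loss.* Take 24 of 80 exercise and 8 of 80 control participants uncounted, and an equal true risk of 20%. The observed risks are 56 × 0.20 / 80 = 14% and 72 × 0.20 / 80 = 18%. Exercise looks safer when it is not.

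All of these overstate the likely loss, because events before drop-out are captured and the repository check may find others.

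**The case against.** The strongest reply is that verification can cover completeness as well as confirmation, and nothing restricts it to reported events. The AE list supports this: death cannot be self-reported, and doubling of creatinine needs a laboratory value, so the authors must have had other sources in mind. Calls go to all participants, every analysis is by intention to treat, and the coordinator tracks withdrawals and follows up missing outcome testing. Leaving the exercise program is not the same as being out of contact. Finally, a condensed article may leave follow-up after withdrawal, and consent to record access, to the full protocol.

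Much of this stands. A reader might infer that the record serves solely to confirm reports, that events after drop-out will certainly go uncounted, or that a fifth of the sample is lost to safety follow-up. The document supports none of these. It does not exclude a wider search or end follow-up at drop-out. It also sets drop-out (below 20%) and missing outcome data (below 10%) as separate feasibility criteria. Nor does it name AEs among the inputs to the later multi-center trial.

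The direction of any bias is open too. An injury or syncope that causes withdrawal precedes it and may well be recorded. Exercise participants also have extra contact (weekly supervised sessions, then kinesiologist calls every 2 weeks), which could raise reporting in that arm.

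What the reply does not remove is the stated method. The article does not leave AE ascertainment open: it gives self-report plus verification, in the text and again in the table. A list that presupposes other sources is a reason to name them.

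**Conclusion.** The point holds as a limitation of the stated method that is cheap to correct. It is neither a contradiction nor a demonstrated loss of events. As written, AEs come from participant contact and the repository verifies them. Major AEs in people who can no longer be contacted may therefore be missed and treated as non-events in the between-arm comparison, possibly to different degrees by arm.

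Its size cannot be computed from the document. The shares of 20% and 33% are upper bounds that assume 32 participants contribute no AE data, at equal and doubled risk respectively. The 14% against 18% result further assumes a 24 to 8 split of that loss. They show what could happen and are not estimates. The conclusion also assumes that all randomized participants form the denominator for AEs, which intention-to-treat implies but the AE sentence does not spell out.

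**What to change.** In the section on baseline clinical information and study visits, and in the adverse events row of Table 1, replace the verification wording with a scheduled search:

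- At 8 and 24 weeks, the electronic health repository is searched for death, unplanned hospitalization, emergency department visits and cardiovascular events in every randomized participant, whether or not still attending, covering the period through week 24.
- The search is the same in both arms and does not depend on a prior report.
- Events found this way are counted in the AE comparison.
- Record follow-up continues after withdrawal from visits unless the participant refuses record access.
- Self-report remains the source for minor AEs.

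The sample size and design do not change. The cost is a few extra look-ups in a repository the trial already plans to use. Recruitment from one provincial renal program, and the exclusion of people planning to move within 9 months, should help coverage. Two limits remain: the search depends on consent to passive follow-up, and on what the repository holds. The article describes it as a provincial source containing pharmacy records and as the check on AEs, but does not list its contents, so the team should confirm that deaths, admissions and emergency visits can be found there.
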